**Figure 2 figure2:**
[figure not shown]
Example of The Good Talk! game interface on a web browser.

### Design

Participants who enter the game website and agree to participate in the research study will be randomized to the experimental or control group (between subjects) and complete both a pre- and postgame survey (within subjects). The experimental group will play *The Good Talk!* game, and the control group will play the noneducational game *Tetris*.

### Outcome Measures

#### Prior Experience With COVID-19 Vaccination

Participants will be asked whether they have had or are currently supportive of people getting the COVID-19 vaccination, whether they currently know someone who is hesitant toward getting the COVID-19 vaccination (and if so, their relationship with this individual), and whether they have previously tried to have a conversation about COVID-19 vaccination with a vaccine-hesitant individual.

#### Self-efficacy

Participants will rate how confident they are to be able to start a conversation about COVID-19 vaccination with a vaccine-hesitant individual on a 7-point scale ranging from “not at all confident” to “very confident.” The self-efficacy item will be asked in the pre- and poststudy surveys.

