### Overview of Intervention Hypotheses

In the previous sections, we have detailed the theoretical development of *The Good Talk!* intervention. Our next step is to conduct a research study to evaluate the efficacy of *The Good Talk!* serious game to improve people’s skills and competences to have open conversations about COVID-19 with vaccine-hesitant individuals. In the following sections, we present a detailed research protocol describing the planned evaluation study to be conducted along with the implementation of the game. Once completed, the results of the evaluation study will be reported in a separate publication.

The efficacy of the intervention game will be evaluated in a preregistered randomized controlled trial. Specifically, we aim to answer the following research question: “How well does *The Good Talk!* game improve people’s open conversation skills, perceptions of self-efficacy, and behavioral intentions to have open conversations with vaccine-hesitant individuals who are close contacts?” We will compare a group of participants who play the intervention game with a control group that will play the widely known noneducational game *Tetris*. *Tetris* was selected as the game for the control condition as it is in the public domain, and most people know how to play it without the need for practice or instruction. *Tetris* involves a similar amount of cognitive effort to play as the intervention game, it contains no content related to the study, and it has been used as a control game to validate other digital game-based learning interventions [62,94,105]. *Tetris* is an inactive control group (receiving no educational material), which is an appropriate design for assessing the absolute efficacy of the intervention [106].

Our primary hypothesis is as follows:

*Hypothesis 1: Relative to the control group, The Good Talk! game will result in a greater increase (boost) in participant’s skills to have an open conversation with a vaccine-hesitant individual*.

We also hypothesize the following:

*Hypothesis 2: Relative to the control group, The Good Talk! game will result in a greater increase in individual’s feelings of self-efficacy to have an open conversation with a vaccine-hesitant individual*.*Hypothesis 3: Relative to the control group, The Good Talk! game will result in a greater increase in intentions to have an open conversation with a vaccine-hesitant individual*.

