The remaining 4 chapters see the participants encounter characters within their close ties who are motivated by reactance (negative affective reaction when one feels personal freedoms are being threatened), skepticism (doubting knowledge or claims), and inertia (opposing change or action) when discussing COVID-19 measures for the social event. As the conversation develops, the player must select from ≥2 conversational responses that affect the participant’s pathway toward the game objective and the points they earn on a Good Talk Meter. The Good Talk Meter increases with response choices that represent good open conversation skills and decreases for those that represent bad open conversation skills. In each chapter, participants are guided by a *Good Talk Guide* who offers advice and reinforces or educates participants about the strategies based on their selections. A brief description of the objective of each chapter is provided in Table 1, and a screenshot of the game interface is shown in Figure 2.

**Table 1 table1:** Brief overview of the goal and open conversation skills for each chapter.

Chapter	Goal
Introduction	The participant is introduced to the objective of the game and asked to select an avatar and an event they would like to plan. An overview of *The Good Talk!* skills is provided to participants along with the definition of what it means to have an open conversation.
Gain trust	The participant converses with someone who is worried about their kids not being vaccinated and whose kids are skeptical about the government’s use of COVID-19 antigen tests. The participant is encouraged to gain the trust of the conversation partner and, in turn, to encourage their partner to use open conversation skills to gain the trust of their children by expressing their concerns, finding mutual value, and supporting their kid’s autonomy.
Offer support	In this chapter, the conversation partner mistrusts the seriousness of the pandemic, is skeptical about the evidence, and does not see a personal need to get vaccinated. The participant is encouraged to ask for the perspective of their conversation partner rather than argue, with the goal to understand their views and to continue the conversation. By acknowledging their partner’s perspective and concerns, the participant is encouraged to find some common ground so that both feel comfortable attending the event.

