#### Behavioral Intention

Participants will be asked to indicate how likely it is that they will start an open conversation about COVID-19 vaccination with a vaccine-hesitant individual in the next 4 weeks on a 7-point scale ranging from “I will definitely not start a conversation” to “I will definitely start a conversation.” Consistent with recommendations for assessing intentions, the measure uses a likelihood scale and defines a timeframe for the behavior [109,110]. The behavioral intention item will be asked in the pre- and poststudy surveys.

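### The self-efficacy item, as described, leaves out the word open, so it covers the construct in Hypothesis 2 only in part

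*Protocol article*

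**What the plan says.** Under Overview of Intervention Hypotheses, Hypothesis 2 predicts a "greater increase in individual’s feelings of self-efficacy to have an open conversation with a vaccine-hesitant individual" relative to the control group. The abstract attaches the same object, an open conversation, to both secondary outcomes.

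Under Outcome Measures, the Self-efficacy section describes one item on a 7-point scale, asking "how confident they are to be able to start a conversation about COVID-19 vaccination with a vaccine-hesitant individual". It is given twice: "The self-efficacy item will be asked in the pre- and poststudy surveys".

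The Behavioral Intention section follows directly. Its stem asks "how likely it is that they will start an open conversation about COVID-19 vaccination with a vaccine-hesitant individual in the next 4 weeks". Its response scale is described as "ranging from “I will definitely not start a conversation” to “I will definitely start a conversation", so the stem specifies an open conversation and the anchors do not. The Implementation Intention section again refers to an open conversation.

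**The concern.** The qualifier carries the content of the intervention. The game does not try to make people talk about vaccination in whatever manner they like. It teaches a particular manner, and one of its eight skills is to avoid lecturing or persuading. The primary outcome depends on telling open replies from replies that are not open.

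An item that asks only about starting a conversation does not draw that line. Two readings of the result are then weakened:

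- If the arms do not differ, one explanation is that participants already felt able to start some kind of vaccination conversation, which says little about an open one.
- If the game arm rises more, the rise does not by itself show greater confidence in holding an open conversation, which is what Hypothesis 2 asserts.

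Self-efficacy rests on this one item, so no other item in a scale can make up for the missing qualifier.

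**Working it through.** No arithmetic bears on this point, so the check is to set the wordings side by side.

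| Place in the article | Act | Open specified? |
|---|---|---|
| Abstract, secondary outcomes | have | yes |
| Hypothesis 2 | have | yes |
| Self-efficacy item | start | no |
| Behavioral Intention, stem | start | yes |
| Behavioral Intention, anchors | start | no |
| Implementation Intention | have | yes |

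**Step 1: is the change from having to starting a fault?** No. The Intervention Goal section explains it: starting an open conversation is a concrete behavior, whereas having one is less well defined. The intention stem follows that reasoning.

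**Step 2: does the same explanation cover the loss of the word open?** No. The behavior that section singles out as concrete is starting an *open* conversation. The argument accounts for the verb and leaves the qualifier in place.

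**Step 3: does the qualifier separate real cases?** Yes. In Table 2 the bad responses are also exchanges about COVID-19, its vaccines or the related measures. Under the skill of not lecturing, the bad example asks whether the partner has looked at the data and then asserts that the side effects are minor. A person who feels sure of conversing like that could honestly give a high rating to the item as described, yet not hold the confidence that Hypothesis 2 is about.

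**Step 4: how much of the construct is still covered?** Most of it. The item shares the topic (COVID-19 vaccination), the partner (a vaccine-hesitant individual) and the act (starting) with the target behavior. Only the manner of the conversation is missing.

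**Step 5: does anything else depend on the wording?** No. The sample size was set for the primary outcome. With f = 0.18, one numerator degree of freedom and noncentrality 327 × 0.18² = 10.59, the noncentral F distribution gives power 0.9007 at N = 327, which reproduces the article's figure. None of these inputs involves the self-efficacy item.

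**The case against.** The best defense has three parts.

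First, the article describes the item; it does not print it. The short form is used elsewhere for what is plainly the same behavior: the intention anchors drop the qualifier that their own stem carries, and the Discussion speaks of initiating conversations about vaccination. The fielded item may already say open. This stands as a possibility. It changes which text needs correcting, but not the need to reconcile the texts.

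Second, the theory sections themselves state the self-efficacy target loosely. The Intervention Goal section describes advocates who lack the self-efficacy to start a conversation, and aims at their readiness to approach such conversations instead of avoiding them. On that view the item measures what the designers had in mind, and the quality of the conversation is left to the primary outcome. This also stands, and it is why the item must be credited with substantial overlap. It does not remove the mismatch, because the hypothesis to be tested names an open conversation.

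Third, the consequence is small: one secondary outcome. That is correct.

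A reader might go further in three directions that the document does not support:

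- **Close contacts.** The research question mentions them and the item does not. But Hypotheses 1 to 3 refer only to a vaccine-hesitant individual, and on this the item matches its hypothesis.
- **An unshared definition.** Table 1 says the game's introduction gives an overview of the skills "along with the definition of what it means to have an open conversation", and one might infer that controls must answer about an unexplained term. The survey instructions are not shown, so this cannot be established. *Tetris* was also chosen deliberately as a control without educational content, so teaching the concept is part of the contrast being tested.
- **A size for the ceiling effect.** The article gives no baseline distribution for the item and no expected effect on self-efficacy, so any such figure would be invented.

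**Conclusion.** The point holds as a mismatch between a secondary outcome and its hypothesis. As described, the self-efficacy item measures confidence in starting a vaccination conversation, of which confidence in starting an open one is only a part. A reader might infer that Hypothesis 2 is not measured at all. That is too strong, given the shared topic, partner and act.

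The effect on the result cannot be quantified from the document. It is limited to the interpretation of one single-item secondary outcome. The conclusion assumes that the Self-efficacy section reflects the fielded wording; if it does not, what remains is an error in the description.

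**What to change.** Before recruitment, word the self-efficacy item in both surveys as confidence to start an *open* conversation about COVID-19 vaccination with a vaccine-hesitant individual. If the instrument already reads that way, correct the Self-efficacy section. In either case add the same qualifier to both anchors of the Behavioral Intention scale, so that stem and anchors name one behavior. Check that the preregistration carries the same wording.

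The cost is a few words in two items, and a note to the ethics committee, whose approval is described as pending, if the submitted survey text changes. The article places the start of data collection in the future, so the edit is cheap at that stage. Once pretest responses exist, the item cannot be changed without losing comparability between the two surveys.

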#### Behavioral Intention

Participants will be asked to indicate how likely it is that they will start an open conversation about COVID-19 vaccination with a vaccine-hesitant individual in the next 4 weeks on a 7-point scale ranging from “I will definitely not start a conversation” to “I will definitely start a conversation.” Consistent with recommendations for assessing intentions, the measure uses a likelihood scale and defines a timeframe for the behavior [109,110]. The behavioral intention item will be asked in the pre- and poststudy surveys.

#### Implementation Intention

Following the behavioral intention item in the poststudy survey, participants will be asked to plan their intention. Implementation intentions refer to intentions to enact a preplanned behavior and can mentally simulate the process of implementing a goal, aiding goal striving [110-112]. Participants will be asked to indicate which vaccine-hesitant individual they plan to have an open conversation about COVID-19 vaccination with (eg, a family member, friend, coworker, or someone else or indicate that they have no plan to have an open conversation with a vaccine-hesitant individual), when they plan to have the conversation (eg, in the next ___ hours/days/months), and to specify what their starting sentence will be.

#### Open Conversation Skills

Participants will be provided with conversation snippets presented as messenger app messages and asked to rate each statement according to how good or bad they think the response is when having an open conversation on a 5-point scale ranging from “very bad” to “very good.” Participants will rate 8 conversation snippets in the prestudy survey and a different set of 8 conversation snippets in the poststudy survey. Using parallel versions of pre- and postintervention tests in the evaluation of serious games reduces practice effects [106,113]. In each survey, there will be 1 conversation snippet for each of the 8 open conversation skills (Table 2). For each open conversation skill, one item will represent a bad response example and the other will represent a good response example. Good and bad response examples for a single open conversation skill will not appear in the same survey. The open conversation skill snippets were reviewed by experts in behavioral science interventions.

**Table 2 table2:** Examples of good and bad open conversation skills included in the pre- and poststudy measure.

Objective and skill		Good response	Bad response

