**Build trust**			
	Find mutual value	I am worried about the safety of the vaccine for my family. What if it made them sick?^a^ Response: I’m concerned about my family’s health too and also feel responsible if something bad was to happen to them.	Hey, so I’m unvaccinated but I’m still gonna go over to my friend’s house who is really strict about people being vaccinated. Response: Hmn, that’s not something I would do. I would respect other’s decisions.
	Respect autonomy	I can’t believe the government is suggesting that everyone should get vaccinated. This is my health, my decision. Response: The choice is yours and only you can make it. What would help you make your decision?	These COVID regulations are ridiculous, next thing you know I’ll have to wear a hazmat suit to go shopping.^a^ Response: You should respect other people’s health and follow the regulations.
	Don’t lecture or persuade (don’t be an expert)	How can they even be sure the vaccine is safe if they made it so fast? It was rushed, who knows what steps they missed!^a^ Response: I think it might have something to do with reducing all the red tape that helped speed things up but I’m not sure. Let’s look into it together!	I am concerned about the side-effects of the vaccine. I heard that they can get pretty bad. Response: Have you looked at the data? I have, and the side-effects are minor. You should look into what can happen if you don’t get the vaccine.

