**Offer support**			
	Ask for perspective	My friend has a party but she says I need to be vaccinated to go, not sure how I feel about it? Response: What makes you unsure?	I don’t believe getting a booster vaccine is really necessary.^a^ Response: It’s interesting how you justify putting other people at risk.
	Affirm feelings or perspective; acknowledge past efforts or successes	I’m unsure about whether to take the vaccine, it seems dangerous.^a^ Response: It is good that you are critical and don’t rush into things when you are unsure. Remember when you had to switch to that new medication and felt better when you looked into it more?	Our neighbours were strict with the social distancing thing and one of them got it anyway. And they are both vaccinated! So I just don’t see the point. Response: That’s not how to think about it. Just because they got it doesn’t mean it’s not worth you making any effort.

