**Open up**			
	Ask open questions	For now, I don’t want to get the vaccine. Just because everyone else has decided to get it, doesn’t mean that I have to as well. Response: If you were to consider getting the vaccine, what would change your mind?	How would a mask even help against a virus?^a^ Response: Did you look at the evidence?
	Be resilient if the other is right	First we were told not to bother with masks, and then we were told to wear masks everywhere! These backflips don’t help.^a^ Response: That’s true, the changing recommendations about wearing masks did not help. It goes to show how uncertain things were at the beginning.	I’m waiting, that’s all. It takes time to make sure that the vaccine is safe for everyone. Response: Yeah I’ve heard that point before but let’s focus on why it is important that all healthy people should get vaccinated.

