**Don’t be sad if it doesn’t work out**			
	Accept negative outcomes (the conversation may not work out)	It’s clear that you and I are not on the same page about this. I have my reasons, you have yours. Response: That’s OK, thanks for helping me understand your reasons. It seems like it doesn’t work out, so let’s leave it there and maybe we can speak again next week?	Look I just don’t think we are ever going to agree on this.^a^ Response: You don’t appreciate my views! But give me one more try and I bet I can change your mind on this one.

^a^Items included in the prestudy survey.

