## Results

Recruitment and data collection are estimated to commence in early 2023. The efficacy of the study will be analyzed using an analysis of covariance with posttest open conversation skills as the dependent variable, controlling for pretest scores. Partially completed surveys will be included in statistical analysis whenever possible. As a sensitivity check, analyses will be repeated by excluding participants who complete the study less than 2 SDs below the median completion time as a data quality check.

The primary outcome is open conversation skills. The secondary outcomes are self-efficacy and behavioral intention items. Exploratory analyses will examine the effect of the game on implementation intentions as well as potential covariates or subgroup differences based on sociodemographic information or previous experiences with COVID-19 vaccination conversations.

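### In the posttest skills form all four good replies end in a question and no bad reply does, so a gain on the primary outcome could largely reflect learning that questions are good

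*Protocol article*

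**What the plan says.** Under Outcome Measures, Open Conversation Skills, participants rate eight message snippets before the game and eight different ones after it, on a 5-point scale from very bad to very good. Each form has one snippet per skill. On keying, the section says: "For each open conversation skill, one item will represent a bad response example and the other will represent a good response example". A skill's good and bad items never share a form. Table 2 prints two replies for each of the eight skills, and its footnote a marks those used in the pretest. The caption speaks of examples, but 8 × 2 = 16 items is exactly the number that the two forms need.

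The Results section states that "The primary outcome is open conversation skills" and that the analysis is an "analysis of covariance with posttest open conversation skills as the dependent variable, controlling for pretest scores".

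The skills section lists open questions as a skill under *Open up* and asking for the other person's perspective as a skill under *Offer support*. Table 1 gives each of them a game chapter. According to Overview of Intervention Hypotheses, the control game has no content related to the study.

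**The concern.** The posttest score is the dependent variable of the primary analysis. If one feature of the replies' form lines up with the key in the posttest, a participant can score well by responding to that feature, without judging each skill. The feature here is a closing question, and only one arm is taught to value questions. A difference between arms would then be open to two readings: better judgement across eight skills, or one simple lesson. Hypothesis 1 is about skills to hold an open conversation, so the reading matters for what the trial can claim.

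**Working it through.** **1. The plan's own figure.** Participants and Recruitment gives f=0.18, power 0.90 and α=.05 for the analysis of covariance, with a total of 327. Noncentral F with two groups, one covariate, numerator df 1 and λ = f²N gives N=327 (power 0.9007). The figure reproduces. For two equal arms f=0.18 is d = 2 × 0.18 = 0.36.

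**2. Posttest replies (no footnote a).**

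| Skill | Key | Ends in a question? |
|---|---|---|
| Respect autonomy | good | yes: "The choice is yours and only you can make it. What would help you make your decision" |
| Ask for perspective | good | yes: "What makes you unsure" |
| Ask open questions | good | yes: "If you were to consider getting the vaccine, what would change your mind" |
| Accept negative outcomes | good | yes: "leave it there and maybe we can speak again next week" |
| Find mutual value | bad | no |
| Don't lecture or persuade | bad | no (it opens with a question) |
| Affirm feelings or perspective | bad | no |
| Be resilient if the other is right | bad | no |

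Each quoted reply closes with a question mark in Table 2. Correctly sorted by the closing-question rule: 4 good + 4 bad = 8 of 8. If the rule is that the reply contains a question, the *Don't lecture* item is missorted: 4 + 3 = 7 of 8.

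**3. Pretest replies (footnote a).** One good reply of four ends in a question (*Affirm*), and so does one bad reply of four (*Ask open questions*: "Did you look at the evidence"). Correctly sorted: 1 + 3 = 4 of 8, no better than chance, under either coding.

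**4. How far allocation explains it.** Each form takes four skills in their good version and four in their bad version, so there are C(8,4) = 70 possible allocations. For 8 of 8 at posttest, *Find mutual value*, *Don't lecture* and *Be resilient* must appear in their bad version and *Ask open questions* in its good version. Three of the remaining four skills then appear in their good version: C(4,3) = 4 allocations of 70. The plan uses one of these. Over all 16 items the rule sorts 5 good + 7 bad = 12, so the two forms always total 12, and the best even balance is 6 and 6.

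**5. What a shift would do.** The article prints no scoring rule, so assume a mean of eight items keyed by label. If ratings of question-ending replies rise by s and nothing else changes:

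- Posttest: change = 4s/8 = s/2.
- Pretest: +s on one good item and −s on one bad item after keying; change = 0.

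Setting s/2 = 0.36 × SD gives s = 0.72 × SD. The SD is not in the documents. For assumed values:

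- SD 0.4: s = 0.29
- SD 0.5: s = 0.36
- SD 0.6: s = 0.43

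**The case against.** The strongest defence is that both randomised arms rate the same form. The between-arm test keeps its type I error, the sample size is right, and Hypothesis 1 does not claim a gain skill by skill. All of that stands. In two of the four good items (*Ask for perspective* and *Ask open questions*) the question is the skill itself, so rewarding it there is proper. That stands too, but *Respect autonomy* and *Accept negative outcomes* can be shown without a question.

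A reader might infer that one cue earns the full primary score. The documents do not support that as stated. It needs the rule to be about the last sentence, a keyed sum or mean that the article does not print, and a participant who rates every statement reply very bad. The rule that the game more plausibly teaches sorts 7 of 8: replying with a question fails on *Don't lecture*, and asking open questions fails on *Accept negative outcomes*, whose closing question is not an open one.

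A reader might also infer that no later analysis could help. That is too strong. If the game raised only the question replies, separate results for good-keyed and bad-keyed items would show a gain confined to the good-keyed ones. They would not show whether that gain came from the question or from the skill. The free-text starting sentence, collected with the implementation intentions, gives some further evidence that does not depend on these items.

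Finally, the shift in step 5 shows how small a change would suffice, not that it will happen. A rise of the same size on any four items would give the same result.

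**Conclusion.** The concern holds as a limit on interpretation. In the posttest form, key and closing question coincide on 8 of 8 items (7 of 8 under the looser coding), against 4 of 8 at pretest, and question asking is trained in one arm only. Under any keyed sum or mean, a between-arm gain could largely reflect learning that questions are good. Adjusting for the pretest cannot correct this, because the cue nets to zero there and baseline scores do not capture what is learned afterwards.

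The size of the distortion is unknown. A rise of 0.29 to 0.43 point on four replies would equal the planned effect, given an assumed SD of 0.4 to 0.6 and mean scoring. It would be wrong to conclude that the trial or its test is invalid: the randomised comparison and N=327 stand, and a real gain across skills remains possible. This should be fixed before launch, while it is cheap.

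**What to change.** Reword posttest replies so that question endings are balanced across good and bad items. For example, drop the closing question under *Respect autonomy* and *Accept negative outcomes*, and end two bad replies with a closed or leading question. The cue then sorts 2 good + 2 bad = 4 of 8. Have the same expert reviewers recheck the keys of the changed items, and update the preregistration.

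If wording cannot change, exchange *Ask open questions* and *Be resilient if the other is right* between the forms. The cue then sorts 3 + 3 = 6 of 8 at posttest and 2 + 4 = 6 of 8 at pretest, the best even balance that reallocation allows. Report the primary effect separately for question and non-question replies as well. This lessens the problem without removing it.

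The cost is a few reworded survey lines or one exchange of items, a repeat item check and a preregistration update. The sample size does not change.
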